## Abstract

**Background:**

Chronic heart failure is characterized by an inability of the heart to pump enough blood to meet the demands of the body, resulting in the hallmark symptom of exercise intolerance. Chronic underperfusion of the peripheral tissues and impaired nitric oxide bioavailability have been implicated as contributors to the decrease in exercise capacity in these patients. nitric oxide bioavailability has been identified as an important mediator of exercise tolerance in healthy individuals, but there are limited studies examining the effects in patients with chronic heart failure.

**Objective:**

The proposed trial is designed to determine the effects of chronic inorganic nitrate supplementation on exercise tolerance in both patients with heart failure preserved ejection fraction (HFpEF) and heart failure reduced ejection fraction (HFrEF) and to determine whether there are any differential responses between the 2 cohorts. A secondary objective is to provide mechanistic insights into the 2 heart failure groups’ exercise responses to the nitrate supplementation.

**Methods:**

Patients with chronic heart failure (15=HFpEF and 15=HFrEF) aged 40 to 85 years will be recruited. Following an initial screen cardiopulmonary exercise test, participants will be randomly allocated in a double-blind fashion to consume either a nitrate-rich beetroot juice (16 mmol nitrate/day) or a nitrate-depleted placebo (for 5 days). Participants will continue daily dosing until the completion of the 4 testing visits (maximal cardiopulmonary exercise test, submaximal exercise test with echocardiography, vascular function assessment, and vastus lateralis muscle biopsy). There will then be a 2-week washout period after which the participants will cross over to the other treatment and complete the same 4 testing visits.

**Results:**

This study is funded by National Heart Foundation of Australia and Victoria University. Enrolment has commenced and the data collection is expected to be completed in mid 2018. The initial results are expected to be submitted for publication by the end of 2018.

**Conclusions:**

If inorganic nitrate supplementation can improve exercise tolerance in patients with chronic heart failure, it has the potential to aid in further refining the treatment of patients in this population.

**Trial Registration:**

Australian New Zealand Clinical Trials Registry ACTRN12615000906550; https://www.anzctr.org.au/Trial/Registration/TrialReview.aspx?id=368912 (Archived by WebCite at http://www.webcitation.org/6xymLMiFK)

## Introduction

### Background

Chronic heart failure (CHF) is a condition characterized by the inability of the heart to pump sufficient blood to meet the metabolic demands of the body. Affecting over 23 million people worldwide, this disease is the leading cause for hospital admission in both Europe and the United States [1]. CHF is a multifarious syndrome that presents with different physiological impairments depending on age, medical history, pathology, and left ventricular ejection fraction status [2]. Although the etiology of CHF may vary, patients are all plagued by the hallmark symptoms of exercise intolerance (low aerobic capacity), dyspnea, and fatigue [3].

Exercise intolerance, defined by a reduced peak oxygen uptake (VO_2peak_), independently predicts morbidity and mortality and directly contributes to a reduced quality of life in patients with CHF [4-6]. In comparison with healthy controls, patients with CHF have significantly lower VO_2peak_ (~13.5ml/kg/min vs ~23.8ml/kg/min), with accompanying reductions in cardiac output (CO) by 52-53% during maximal exercise [7-9]. Although it was historically assumed that this inability to augment CO during exercise was the primary contributor to exercise intolerance, more recent investigations suggest that resulting under-perfusion of the peripheral muscular tissues may have a more detrimental impact [3,10].

Following acute heart failure, there is an increased activation of the sympathetic nervous system (SNS), which leads to vasoconstriction of arteries supplying blood to the peripheral tissues to defend central blood pressure and vital organ perfusion [10]. Although this SNS response is critical initially, continued overactivation results in chronic underperfusion of the skeletal muscle tissues, thereby contributing to capillary density rarefaction and a preferential loss of type-I oxidative fibers, and thus shifting these patients to a more glycolytic phenotype [11-14]. In the heart and skeletal muscles, there are significant abnormalities in the mitochondrial function, leading to decreases in oxidative phosphorylation [15]. Within the vasculature, a reduction in nitric oxide (NO) bioavailability is also highly prevalent in CHF and has been correlated with both the severity of CHF and the patients’ functional capacity [16]. NO is a key regulator of blood flow and as large and small vessel vasodilation is a crucial contributor to exercise capacity, the inability of patients with CHF to up-regulate NO could be a limiting factor in their exercise tolerance [3,17]. This knowledge has brought about a fundamental shift in the treatment focus for CHF, whereby interventions are now targeting improvements within the peripheral tissue function to restore exercise tolerance.

One emerging therapeutic approach is supplementing with dietary inorganic nitrate (found in kale, green leafy vegetables, or beetroot juice [BTR]) to increase circulating NO bioavailability [18]. This occurs via a 2-step process, whereby nitrate is swallowed and absorbed via the gut and released into circulation. Approximately 25% of nitrate becomes highly concentrated in the salivary glands, which is then secreted and subsequently reduced via oral commensal bacteria to nitrite, which is then swallowed and absorbed into the circulation [19]. The circulating nitrite in the plasma may act as a relatively protected NO species that can be reduced to NO in low-oxygen environments (such as in tissues with low partial pressure of oxygen or during exercise).

Studies in healthy populations have demonstrated a myriad of benefits in exercise performance following nitrate supplementation, including increases in time to exhaustion, oxygen consumption efficiency (during submaximal exercise), total power output, and decreased systemic blood pressure [20-27]. Inorganic nitrate supplementation has even greater potential efficacy in clinical populations as supplementation may be an effective way of assisting in the targeted redistribution of blood flow in the underperfused peripheral tissues [18]. However, in contrast to the numerous studies in healthy populations, there are relatively few studies to date that have examined the effects of inorganic nitrate supplementation on exercise capacity in clinical patients, and only 4 have been on the CHF population [28-31]. A further limitation in our current understanding of inorganic nitrate supplementation in patients with CHF is the lack of substantial evidence in each of the 2 individual classifications of CHF, with a large proportion of the publications focusing only on one classification.

Currently, there are 2 classifications for patients with heart failure differentiated by whether the patient has a preserved ejection fraction (HFpEF, also known as diastolic dysfunction) or a reduced ejection fraction (HFrEF, also known as systolic dysfunction). HFrEF often results from an acute ischemic event that causes tissue death, leaving the cardiac muscle less able to contract adequately. In these patients, the ejection fraction is reduced because of left ventricular chamber dilation [32,33]. Patients with HFrEF have a lower CO both at rest and during exercise as compared with HFpEF patients and healthy controls [8]. HFpEF typically has a slower onset and these patients are more likely to be older, female, and suffer from a myriad of other comorbidities. Although they also have significant left ventricular remodeling, in HFpEF, the chamber size remains unchanged, but there are increases in the wall thickness and the ratio of ventricular mass to chamber volume. These maladaptations lead to significant elevations in LV filling pressures, which is known to cause exertional dyspnea and further contribute to exercise intolerance [34]. Additionally, the impaired arterial hemodynamic profile of these patients (increased arterial stiffness, reduced exercise induced vasodilation) creates a unique model for which a vasodilatory intervention, such as inorganic nitrate supplementation, could be very effective [35,36].

In CHF, the HFpEF cohort has been the most studied. Zamani et al provided acute supplementation of inorganic nitrate in the form of beetroot juice (12.9 mmol nitrate) to 17 HFpEF patients and saw improvements in total time to exhaustion (TTE) and VO_2peak_ during a maximal exercise test [29]. The performance benefits were accompanied by an increase in CO, although this was secondary to a decrease in systemic vascular resistance [29]. Following chronic inorganic nitrate dosing, Eggebeen et al found that 6.1 mmol nitrate/day for 7 days (in the form of beetroot juice) led to a 24% increase in TTE during an exercise bout of cycling at 75% of each individual’s maximum power output [28]. Similarly, Zamani et al identified significant increases in TTE following a 2-week potassium nitrate dosing regimen (6 mmol/day for 1 week, increasing to 18 mmol/day for the second week) [37]. These studies lend support to inorganic nitrate supplementation’s potential efficacy for improving exercise tolerance in patients with HFpEF; however, the small sample sizes and limited mechanistic data leave plenty of scope for future studies.

In comparison with the positive results seen in HFpEF cohorts, data for HFrEF remains limited. A recent study by Hirai et al supplemented HFrEF patients with 12.9 mmol nitrate/day in the form of beetroot juice for 9 days and reported no changes in any of the parameters examined, including exercise performance, central hemodynamics, and blood pressure [31]. The authors suggest that the negative findings could be because HFrEF patients have relatively normal oxygen extraction rates within the peripheral tissues. Although Hirai et al is the only human study examining the effects of inorganic nitrate supplementation on exercise capacity in patients with HFrEF, Coggan et al conducted a study examining the effects of nitrate supplementation on isokinetic knee extensor power [30]. This study showed a 13% increase in the maximal power output following a single dose of inorganic nitrate (11.2 mmol). The authors suggested that the substantial improvement (they note that it is much larger than the 6% increase observed in healthy controls) was due to NO’s known effect of increasing the activation of cyclic guanosine monophosphate. As this activation is known to lead to increases in maximal power output, particularly in type II fibers, it lends further support to nitrate’s efficacy in CHF (where patients are known to be more type II-fiber dominant). In further support of these findings, 2 separate CHF rat model studies, 1 using an acute dose (5 mg/kg sodium nitrite) and 1 using a chronic dose (1 mmol nitrate/kg/day for 5 days), demonstrated significant increases in blood flow and vascular conductance in skeletal muscle [38,39]. The acute sodium nitrite infusion also showed a preferential increase in blood flow, specifically in the muscles of the rats with a higher percentage of both type IIb + IId/x fast-twitch fibers [38]. This further illustrates the potential efficacy of nitrate supplementation within the HFrEF population. Thus, despite the lack of positive findings in the study by Hirai et al, there remains a lot of promise in the use of nitrate supplementation in patients with HFrEF.

Overall, the area of inorganic nitrate supplementation in patients with CHF is relatively new. The current studies have small sample sizes (3 of the 5 human studies had ≤12 participants) that lack diversity in gender (Hirai et al only had male participants) and testing modalities (all exercise studies used cycle ergometry). Moreover, no study to date has sought to examine and compare the effects of nitrate supplementation in HFrEF and HFpEF patients within the same testing protocol. The development of research trials recruiting both HFrEF and HFpEF patients is critical to advancing our understanding of how to best clinically target and treat the mechanistic differences between these 2 distinct classes of CHF.

### Objective

The primary aim of this study is to test the hypothesis that 5 days of inorganic nitrate supplementation (16 mmol/day) will improve exercise tolerance (VO_2peak_ and TTE) in both HFpEF and HFrEF patients. We further hypothesize that patients with HFpEF will have larger improvements in exercise tolerance than patients with HFrEF because of greater impairments in their peripheral muscular tissues. The secondary aim of the project is to identify the mechanistic contributors to exercise tolerance in both heart failure classifications via examining the following outcome measures:

Gastrocnemius tissue oxygenation at rest and during submaximal and maximal exercise via near-infrared spectroscopy (NIRS)Vastus lateralis muscle tissue composition and function (angiogenesis, capillaries per unit area and per muscle fiber, mitochondrial function, and muscle fiber composition)Vascular function via brachial artery flow-mediated dilation, lower-limb blood flow via plethysmography, and pulse wave velocity (PWV) and reflection.

## Methods

### Study Design and Participants

This is a randomized, double-blind, placebo-controlled, crossover study (see Figure 1). Following a screening visit, participants will be randomized to consume either nitrate-rich beetroot juice or a nitrate-depleted placebo for 5 days. Following this 5-day loading, the participants will continue daily dosing until the completion of the 4 testing visits (maximal cardiopulmonary exercise test (CPX), submaximal exercise test with echocardiography, vascular function assessment, and vastus lateralis muscle biopsy). Due to the need for adequate rest days between exercise visits, it could take up to 2 weeks in total to complete all testing visits within each round. However, both the dosing days and testing order will be matched within each participant between the 2 rounds of supplementation. Participants will then have a 2-week washout period before completing the second round of the study.

### Recruitment Strategies and Eligibility

We aim to recruit 15 patients with HFrEF and 15 patients with HFpEF. A total sample of 30 is a realistic number of patients that can be recruited within the time frame of the study (18 months) and is similar to other successful studies in this field [29,40].

Recruitment will be open to individuals between the ages of 40 and 85 years who have diagnosed stable CHF with either HFrEF ≤40% or HFpEF ≥50% with no major changes in medications for at least 3 months (see Textboxes 1 and 2).

**Figure 1 figure1:**
[figure not shown]
Max CPX: maximal cardiopulmonary exercise test; submaximal echo: submaximal exercise test with echocardiograph imaging; vascular testing: resting measures of blood flow and arterial function; and muscle biopsy: vastus lateralis muscle biopsy.

Inclusion criteria.Aged between 40 and 85 yearsDiagnosed stable chronic heart failure (CHF) with either reduced ejection fraction (HFrEF) ≤40% or preserved ejection fraction (HFpEF) ≥50%New York Heart Association class II-IIIOn stable medications for at least 3 monthsPeak VO_2_ <85% of age-predicted maxAdditional criteria for HFpEF recruitmentEvidence of abnormal diastolic filling pressure (eg, abnormal E/e′, abnormal deceleration time, dilated left atrial volume, or elevated brain natriuretic peptide [if available]) [41]Signs and symptoms of heart failure, plus definite episodes of decompensated heart failure (adjudicated via Boston Criteria)

Exclusion criteria.A major cardiovascular event within the previous 6 weeks or a planned hospitalization within the next 2 monthsPatients with an ejection fraction between 41 and 49Uncontrolled diabetes (>9% HbA1C [glycated hemoglobin])—Can delay start of testing by 3 months until levels are controlled and stableFoot ulcers/advanced neuropathy or other musculoskeletal condition that could limit exercise performanceAbnormal response to CPXAllergy to beets or proton pump inhibitorsRefusal or inability to abstain from the use of proton pump inhibitors for 24 hours before testing

Potential participants will be identified through medical chart reviews and will be contacted in person during a hospital or clinic visit. They will be given the contact information for the trial recruitment coordinator and instructed to contact the team if they wish to learn more about the study. At all stages, potential participants will be reminded that their participation in the study is voluntary and that their decision to participate or not will in no way affect their usual care.

### Screening Visit

Patients who wish to participate in the study will be asked to sign an informed consent. They will then complete a screening maximal CPX that will be supervised by a medical practitioner. Although the primary purpose of CPX is to screen for adverse events or contraindications to participation in the study, it will also serve as a familiarization visit for the participants. This CPX employs a 2-step protocol that includes 6 min of low-intensity walking at 1.4 km/hour at a 4% grade. Following this, the speed and/or incline will be increased in an individualized manner as the participants’ capabilities allow until maximal exertion is achieved. The test will only be stopped if the medical practitioner deems it unsafe to continue or the patient requests to stop. The max CPX protocol will be kept constant between visits for each individual subject. Similar protocols have been previously used in this population as the 2-step protocol allows for collection of both submaximal and maximal measures of aerobic capacity and function within 1 exercise bout [42-44].

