### Outcome Measurements

The primary outcome measure will be exercise tolerance [VO_2peak_ and TTE] during the 2-step CPX test. Secondary outcomes will include measures at rest and during exercise for cardiac function (CO, SV, MAP), as well as peripheral tissue function (lower limb blood flow, endothelial function, PWA, PWV, mitochondrial function). In addition, measures of plasma nitrate and nitrite will be recorded for nitrate-nitrite conversion rate calculations.

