### Statistical Analysis

The primary endpoint of this pilot study is exercise capacity (VO_2peak_ and TTE) during the maximal CPX in both the HFpEF and HFrEF cohorts. A repeated-measures *t* test will be conducted to determine the changes in exercise capacity variables in the 2 groups combined. This will be followed by a repeated measure analysis of variance to determine the time×group effect in HFpEF and HFrEF patients. Similar analyses will be performed on the secondary endpoints/variables listed in the Specific Aims. Post hoc comparisons of change scores for relevant variables between HFpEF and HFrEF will be performed. Additional pairwise tests as well as linear regressions between the placebo and beetroot juice conditions will be used to determine what physiological factors (mitochondrial efficiency, endothelial function, tissue perfusion, leg blood flow, CO) contribute to any potential changes in exercise tolerance in HFpEF versus HFrEF.

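### TTE in seconds is not on a common scale across patients because each has their own treadmill ramp, so the HFpEF-versus-HFrEF comparison of TTE changes can show or mask a cohort difference

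*Protocol article*

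**What the plan says.** The Objective section states a directional cohort hypothesis with a cause attached: "patients with HFpEF will have larger improvements in exercise tolerance than patients with HFrEF because of greater impairments in their peripheral muscular tissues". Exercise tolerance is defined by two variables (Outcome Measurements): "The primary outcome measure will be exercise tolerance [VO_2peak_ and TTE] during the 2-step CPX test".

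The test is described under Screening Visit and is repeated at the maximal CPX visit. Everyone starts with "6 min of low-intensity walking at 1.4 km/hour at a 4% grade". After that, "the speed and/or incline will be increased in an individualized manner". The safeguard is within the person: "The max CPX protocol will be kept constant between visits for each individual subject".

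Under Statistical Analysis, a paired test on both cohorts combined is followed by a "repeated measure analysis of variance to determine the time×group effect in HFpEF and HFrEF patients". In addition, "Post hoc comparisons of change scores for relevant variables between HFpEF and HFrEF will be performed". No conversion of TTE to a common scale is named for either between-cohort analysis.

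**The concern.** Holding each patient's ramp constant makes nitrate and placebo comparable within that patient. It does not make seconds comparable between patients. On a gentle ramp a given gain in capacity buys many extra seconds; on a steep ramp it buys few. Ramps are set by capability, and nothing in the article balances their steepness across the cohorts.

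If mean steepness differs, the cohort comparison of TTE mixes the response to nitrate with the choice of ramp. At stake is the second hypothesis, that HFpEF gains more: it could be accepted or rejected on TTE because of how the tests were set up. Ramp differences within a cohort add noise rather than systematic bias; the problem needs a difference in means between cohorts.

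**Working it through.** **Inputs from the article.** First stage 6 min for all; individual ramp afterwards, constant within a patient (Screening Visit). 15 patients per cohort, 15 + 15 = 30 (Recruitment Strategies and Eligibility). VO2peak of about 13.5 ml/kg/min in CHF (Background). The article gives no ramp rate, no SD of change and no power calculation, so it has no figure of its own to reproduce on this point.

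**Assumptions.** Linear ramps of 1, 1.5 and 2 ml/kg/min per minute; VO2 of 9 ml/kg/min at the end of stage 1; SD of change in capacity from 0.5 to 2 ml/kg/min; two-sided 5% test.

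**1. The two planned cohort analyses are one contrast.** With two conditions per patient, the interaction in the repeated-measures ANOVA equals a two-sample comparison of mean change scores. Both inherit the scale of TTE.

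**2. Seconds gained.** TTE = 6 min + (peak − stage-1 VO2) / rate, so change in TTE (s) = 60 × gain / rate. For an equal gain of 1 ml/kg/min:
- rate 1: 60 × 1 / 1 = 60 s
- rate 1.5: 60 × 1 / 1.5 = 40 s
- rate 2: 60 × 1 / 2 = 30 s

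Masking works the same way. A gain of 1.5 at rate 1.5 is 60 × 1.5 / 1.5 = 60 s, the same as a gain of 1 at rate 1.

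**3. Percent change in TTE does not remove it.** With a peak of 13.5 and stage-1 VO2 of 9, TTE before the gain is 6 + 4.5/1 = 10.5 min, 6 + 4.5/1.5 = 9 min and 6 + 4.5/2 = 8.25 min. The same gain is then 1/10.5 = 9.5%, 0.667/9 = 7.4% and 0.5/8.25 = 6.1%.

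**4. The log ratio of ramp-phase time removes the ramp but brings in baseline reserve.** The ratio is (C + gain)/C, where C is peak minus stage-1 VO2. For a gain of 1, C = 4.5 gives log(5.5/4.5) = 0.20, and C = 9 gives log(10/9) = 0.11. Equal gains still look unequal if one cohort is fitter, so this cannot stand alone.

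**5. Effect on the 15 v 15 test.** Two-sample t tests on TTE change were simulated with an identical true gain of 1 ml/kg/min in both cohorts, 40,000 runs per setting. Each range covers two noise models: SD constant in seconds, and SD scaled by the ramp. Percentage of trials declaring a cohort difference:

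| SD of change (ml/kg/min) | Equal ramps | Mean ramps 1.5-fold apart | Mean ramps 2-fold apart |
|---|---|---|---|
| 0.5 | 5 | 42–55 | 75–92 |
| 1 | 5 | 15–18 | 26–39 |
| 1.5 | 5 | 9–11 | 14–21 |
| 2 | 5 | 7–8 | 10–14 |

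Once the ramp is removed and the change is put on the capacity scale, the test returns to its nominal 5%.

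**The case against.** Several points against the concern are fair.

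- **The bias is conditional.** Nothing in the article says that mean ramp steepness will differ between cohorts, or which cohort would be fitter. Both share the same age range, NYHA classes and peak VO2 ceiling. This stands: the direction and size are unknown, and the table shows what could happen, not what will.
- **VO2peak is already a primary variable and goes through the same cohort analysis.** This also stands. VO2peak is not divided by a ramp rate, so only one of the two primary variables is affected.
- **Details can sit in a SAP.** Covariates and sensitivity models may well be there, and their absence is not part of this point. The scale problem is different: the article fixes both the individual ramp and the cohort comparison of a variable measured on it.
- **The article calls the study a pilot and the change-score comparison post hoc.** True, but the cohort difference is a stated hypothesis on TTE and VO2peak.

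A reader might go further and infer that age and sex differences make unequal changes meaningless, since the Background says of HFpEF that "these patients are more likely to be older, female, and suffer from a myriad of other comorbidities". The documents do not support that. The remark is general background, not trial data. Additive age and sex effects cancel in each patient's nitrate-placebo change. If age or sex modifies the effect, the response really is unequal between the cohorts; only its attribution to heart failure type is in doubt. A model with several modifiers would also say little at 15 v 15, where 80% power needs a difference of about 1.06 SD of change.

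**Conclusion.** The point holds for TTE in seconds compared between HFpEF and HFrEF, and only there. Equal gains in capacity give unequal TTE changes when ramps differ, and the planned comparison has no step that deals with it. On assumed linear ramps, a 2-fold difference in mean steepness turns an equal gain of 1 ml/kg/min into 60 s against 30 s. It raises the false-positive rate from 5% to between 10% and 92%, depending on the SD; a 1.5-fold difference raises it to between 7% and 55%. With equal mean ramps there is no bias.

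It would be wrong to infer that the whole cohort comparison fails or that the nitrate effect is in question. VO2peak is untouched, and the test of nitrate against placebo within patients remains valid because each patient's ramp is fixed.

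Separately, only treatment order is randomized. A cohort difference, on any scale, is therefore an association, and the causal clause in the Objective goes beyond what the comparison can show.

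**What to change.** - Base the HFpEF-versus-HFrEF contrast on VO2peak. Support it with peak treadmill workload computed from final speed and grade, with one formula fixed in advance for all patients.
- Keep TTE in seconds for the within-patient nitrate effect only.
- If TTE is compared between cohorts, convert it to a workload scale using each patient's ramp and label the result exploratory. Do not rely on percent change in TTE or on the log ratio of ramp time alone.
- Report the ramps by cohort, so that readers can see whether mean steepness differed.
- Report any cohort difference as an association, not as caused by peripheral muscle impairment.

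Cost: slightly more analysis work and no change to visits or sample size. The article does not say that final speed and grade are recorded, but each patient's ramp must be documented to be repeated, and with the stopping time it gives both. The between-cohort hypothesis would no longer rest on TTE seconds.
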